## Abstract

Background: As the effectiveness on stress urinary incontinence (SUI) prevention of pelvic floor muscle training (PFMT) for pregnant women has been inconclusive, we are planning to conduct a trial to evaluate a video program designed for prevention of SUI developed through combining PFMT with global postural reeducation (GPR). Methods: As a randomized controlled trial, eligible participants will be randomized (1:1) into an exercise group and a control group to perform PFMT regularly following video guidance or with no intervention, respectively. The experimental stage will be from the 16th gestation week (GW) to the 12th month postpartum, with eight appointments at the 16th, 28th, 37th GW, delivery, the 6th week and the 3rd, 6th, and 12th month postpartum. Data will be collected regarding urinary leakage symptoms, the stress test, the modified Oxford Scale, pelvic floor ultrasound, perineal laceration classification at delivery, neonatal Apgar score, and questionnaires (PISQ-12, ICIQ-UI SF, I-QOL, OABSS). The primary outcome is the occurrence of the symptomatic SUI and positive stress test at the 6th week postpartum. Discussion: This protocol is anticipated to evaluate the efficacy of the intervention via video app for the design of a future randomized control trial (RCT). Trial registration: The trial has been registered at Chinese Clinical Trial Registry (registration number: ChiCTR2000029618).

## 1. Introduction

Stress urinary incontinence (SUI) is defined as “involuntary leakage of urine when abdominal pressure increases” [1]. The prevalence of SUI at the 8th week postpartum was reported to be 25.7% [2], which exerts a widespread negative impact on women’s health. Pregnancy and delivery have been proven to play important roles for SUI development because it weakens pelvic floor muscle (PFM) strength [3]. Although reducing delivery injuries is the key to prevent SUI, there is currently no consensus among medical society on the effective method for SUI prevention during pregnancy.

Pelvic floor muscle training (PFMT) has been recommended as the first optional treatment of SUI [4], while the effect of prenatal PFMT on SUI prevention is inconclusive. Reilly et al. [3] conducted a randomized control trial (RCT) with 268 primiparas women, and concluded that women in exercise groups who performed PFMT regularly had lower SUI occurrence at the 3rd month postpartum than the control group. However, Boyle et al. [5] suggested that PFMT during pregnancy did not prevent urinary incontinence according to a systematic literature review and meta-analysis of RCTs. Some authors pointed out that the diversity of different studies on the compliance of the patients to PFMT and the procedural correctness may accounted for the inconsistent results [6,7,8,9,10].There currently is no uniform protocol for PFMT during pregnancy, and the protocols vary widely across publications [6,7,11]. How to have the patients perform PFMT voluntarily with high compliance is still a challenge, and the optimal number of contraction repetitions, the time and duration of PFMT contraction, and the frequency of doing PFMT are the determinants of a PFMT protocol to its effectiveness.

Global postural reeducation (GPR) was projected to correct postural misalignments by stretching the muscle chains. As the spine is a continuous boney structure that is closely associated with abdominal and pelvic dynamics, it is commonly recognized that spine restructure through posture reeducation would benefit the functions of the PFMs. Our previous study demonstrated that the spinopelvic skeletal shape had a close relationship with pelvic floor dysfunction [12]. In 1981, Souchard first developed GPR in France, aiming to keep the normal posture to recover muscular strength. Fozzatti et al. [13,14] recruited SUI patients for treatment by the GPR and PFMT, and demonstrated that both GPR and PFMT were effective alternatives for the treatment of SUI, while GPR was significantly more effective. 

To explore a more effective exercise regimen for SUI prevention, we developed a training program through combining PFMT with GPR training (PGT program) under the collaborative efforts from several urogynecologists and sports experts from Peking University.

Patient’s compliance is another important factor for the effectiveness of PFMT. Face-to-face training is time-consuming and needs frequent visits to relevant facilities, which therefore further decreases the adherence to the training program. In addition, it is quite hard to organize face-to-face training programs during the COVID-19 pandemic. For a long time, what has been bothering the urogynecologists is how to achieve intensive supervision and encourage participants to keep high compliance. Popularization of mobile phones makes almost everyone accessible via mobile devices, which enabled women to connect to the world from at home; thus, a PGT video guidance on mobile apps can create potentiality to enhance the adherence and compliance of the patients who can perform PFMT and GPR at home.

Therefore, an app-based video program was developed with the collaboration of software engineers. The video program tends to guide the patients to do regular PFMT and GPR at home or any private room. To make the patients’ compliance evaluable during the COVID-19 pandemic, we integrated a high-intensive online supervision module into the video program. We conduct this multicenter RCT to evaluate the effectiveness and safety of the video program on the prevention of postpartum SUI. 

## 2. Materials and Methods

### 2.1. Study Overview

The study is designed as a two-arm, parallel, RCT designed following the Consolidated Standards of Reporting Trials (CONSORT). Participants will be recruited from the obstetrics departments of ten hospitals (the centers) including Peking University People’s Hospital, Peking University International Hospital, Peking University Shenzhen Hospital, Beijing Obstetrics and Gynecology Hospital, Fangshan Maternal and Child Health Hospital of Beijing, Fengtai Maternal and Child Health Hospital of Beijing, Mentougou District Hospital of Beijing, Zhengzhou Central Hospital Affiliated to Zhengzhou University, Luohe Central Hospital of Henan Province and The First Obstetrics Hospital of Shanghai. The ten hospitals are selected as the centers because (1) they have enough patients to recruit the minimum number of patients proposed for each center, and (2) the investigators at those centers are knowledgeable and experienced in the identification and treatment of the SUI. 

### 2.2. Inclusion Criteria

Pregnant women will be eligible for recruitment if they are: (1) 20 to 40 years of age, (2) primipara with a singleton pregnancy of less than 16th gestation week (GW), and (3) willing to participate in the study and understand the research procedure well. 

### 2.3. Exclusion Criteria

In the first enrollment examination, participants will be excluded if they were confirmed: (1) having serious complications (including uncontrolled brain, lung, heart, liver, kidney, and mental illness; coagulation dysfunction; or obvious cognitive dysfunction) that may be aggravated by the intervention, (2) having SUI or pelvic floor organ prolapse (POP) according to pelvic organ prolapse quantitation (POP-Q) staging, (3) having history of cervical insufficiency, recurrent miscarriage, and induced labor, (4) unable to finish all follow-ups, (5) infecting COVID-19, and/or (6) unable to provide consent in writing (Figure 1). Each participant will be recorded as “drop off from trial” if she suffers from miscarriage, serious complications, or missed all follow-ups. Cesarean will not be the endpoint of the experimental follow-ups.

### 2.4. Randomization and Allocation Concealment

A randomization list will be created by a statistician from Peking University for each center before the start of the research using SAS 9.4 (SAS Institute, Cary, NC, USA). The numbers of participants in EG and CG are balanced, with a 1:1 ratio, and put into blocks of four. A unique study ID will be given to each participant. 

The randomization result for EG and CG are sealed in the ID-matching envelopes. The grouping details will be concealed to the investigators who will account for group allocation, recruitment, informed consent, and data collection. Eligible women are informed of grouping allocation via opening the sealed envelope after signing the informed consent. It is not feasible to blind to participants, urogynecologists and physiotherapists engaging in the intervention. However, all the investigators to perform patient evaluation and data analysis will be masked.

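### A single published block size of four within each centre lets anyone there who tracks opened allocations know up to one in three in advance, which weakens allocation concealment

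*Protocol article*

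**What the plan says.** All of the following is in the protocol article, section 2.4 (Randomization and Allocation Concealment), unless another section is named.

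- Lists: "A randomization list will be created by a statistician from Peking University for each center before the start of the research". Section 2.1 names ten centres.
- Block size: "The numbers of participants in EG and CG are balanced, with a 1:1 ratio, and put into blocks of four". One size is given, and nothing is said about varying it or withholding it from sites.
- Concealment: "The randomization result for EG and CG are sealed in the ID-matching envelopes". A woman learns her arm when her envelope is opened, after she has signed consent. The section also states that grouping is hidden from the investigators responsible for allocation, recruitment, consent and data collection.
- Blinding: "It is not feasible to blind to participants, urogynecologists and physiotherapists engaging in the intervention". Against that, "all the investigators to perform patient evaluation and data analysis will be masked".
- Eligibility: section 2.2 asks that a woman be willing to take part and understand the procedures well. Section 2.3 excludes a woman who is "unable to finish all follow-ups".

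**The concern.** Sealed envelopes protect an allocation only if it cannot be worked out from those already opened. With a constant block of four and a 1:1 ratio, the end of every block follows from its beginning. The block size is in print, and allocations become known one at a time in enrolment order within a centre, so the information needed for the deduction is generated at the site.

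What is at stake is selection before randomization. A recruiter who knew the next arm could encourage, delay or turn away a particular woman. The eligibility items on willingness, understanding and ability to complete follow-up leave some room for judgement. The article treats compliance as central to whether training works (sections 1 and 3), so there is a motive to prefer committed women for the exercise group.

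The rest of the plan would not repair such selection. Masked assessment guards against biased measurement, intention-to-treat analysis starts only after randomization, and the primary comparison in section 2.9 is a chi-square or Fisher test, which does not adjust for baseline differences.

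**Working it through.** **Inputs.** Block size 4, 1:1, one list per centre (section 2.4); ten centres (section 2.1); 734 women (section 2.8). The article gives no predictability figure to reproduce. Its enrolment total does reproduce: 293 / 0.80 = 366.25, rounded up to 367 per group, and 2 × 367 = 734. Nothing below changes the sample size.

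**Allocations known for certain.** Write E for exercise and C for control. A place is certain when one arm has already used its two places in the block. There are six equally likely orders:

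- EECC and CCEE: places 3 and 4 are certain, 2 each.
- ECEC, ECCE, CEEC and CECE: only place 4 is certain, 1 each.

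Total = 2 × 2 + 4 × 1 = 8 certain places out of 6 × 4 = 24, so 8/24 = 33.3%. Per block this is 1 + 1/3 = 4/3 of 4 places. Over the trial, 734 / 3 = 244.7, about 245. If recruitment were even across centres (an assumption; the article gives no centre targets), 734 / 10 = 73.4 per centre, of which 73.4 / 3 = about 24 would be certain.

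**Best-guess success.** An observer who always names the arm with more places left is right with these probabilities:

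- Place 1: 1/2.
- Place 2: 2/3.
- Place 3: 1/3 × 1 + 2/3 × 1/2 = 2/3.
- Place 4: 1.

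Mean = (0.500 + 0.667 + 0.667 + 1) / 4 = 70.8%, against 50% by chance.

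**Alternatives.** The fixed sizes were enumerated exactly. The random mixes were simulated with 4,000 lists of 74 women, for an observer who knows which sizes are in use but not their order.

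| Scheme | Certain | Best guess correct |
|---|---|---|
| Fixed 4 | 33.3% | 70.8% |
| Fixed 6 | 25.0% | 68.3% |
| Fixed 8 | 20.0% | 66.6% |
| Random 4/6 | 5.5% | 69.1% |
| Random 4/6/8 | 2.3% | 67.8% |

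In the same simulation, fixed 4 gives 32.4% and 70.5%, slightly lower because 74 women fill 18 complete blocks and leave 2 over: 18 × 4/3 = 24, and 24 / 74 = 32.4%. With random 4/6/8, allocations that are certain or more than 90% probable make up 4.9%.

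**Possible bias (illustration only).** Suppose that women steered into the certain places differed in risk of stress incontinence by 5 to 15 percentage points between arms. This range is an assumption; the article gives no such figure. If every certain place were exploited, the bias would be 1/3 × 5 = 1.7 to 1/3 × 15 = 5 points. If a quarter were exploited, it would be 0.4 to 1.25 points. The planned difference in section 2.8 is 25.7% − 15% = 10.7 points.

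**The case against.** The strongest reply is that section 2.4 says grouping is concealed from the staff who recruit and take consent. The people it names as unblinded are participants and those delivering the intervention, who are not described as recruiters. One in three needs an observer who knows the block size and every earlier allocation at that centre in order, and the article does not say that any recruiter does. This stands as a limit on size: one in three is a ceiling, not an expected figure. It does not remove the concern. The same statement covers the investigators responsible for group allocation, envelopes are opened once consent is signed, and no mechanism is described that keeps opened results from those staff.

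A reader might infer that concealment is defeated. The documents do not support that. The lists are prepared in advance by a statistician, the envelopes are sealed and matched to study ID, and opening follows consent. Even a fully informed observer would be uncertain about two thirds of allocations.

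A reader might also point to the weekly Zoom scheduling and training checks (sections 2.5 and 2.6) as the route by which staff learn who is in the exercise group. The timing makes this weak. Enrolment is before the 16th gestation week and exercise starts at the 28th, a gap of at least 12 weeks. For that route to expose later places in the same block, a centre would have to enrol about four women per 12 weeks or fewer. At 73 women that is 73 / 4 × 12 = 219 weeks. The plausible route is the envelope opening itself.

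The room to steer is also limited: most criteria are factual, willingness is the woman's own decision, and the 16-week limit restricts deferral. Finally, varied blocks barely reduce the guessing advantage. That is true and should be said openly. Their benefit lies in removing certainty, which is what makes steering reliable.

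**Conclusion.** The point holds as a weakness in a stated design choice, not as an error or contradiction. With constant blocks of four within centre, up to 33.3% of allocations, at most about 245 of 734, can be known in advance, and concealment is weakened to that extent. The ceiling assumes knowledge of the block size and of all earlier allocations at the centre in sequence. The per-centre count of about 24 also assumes even recruitment. The documents do not show that any recruiter has this knowledge or would act on it, so the actual bias cannot be estimated and may be nil. The change is still worth making, because the exposure is avoidable at little cost and later analysis could not fully remove the bias if it occurred.

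**What to change.** Have the statistician regenerate the unused part of each centre's list with randomly varying block sizes, for example 4, 6 and 8, keeping a separate list per centre. Do not disclose the sizes to the sites. Allocations already made stay as they are.

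This cuts certain allocations from about 33% to about 2%, while best-guess success falls only from about 71% to about 68%. The cost is one new list per centre and replacement of the unopened envelopes. The largest possible arm difference within a centre at any moment rises from 2 (half of 4) to 4 (half of 8). The sample size and the primary analysis are unchanged.

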### 2.5. Interventions

All participants in EG and CG will have same routine obstetric prenatal care following the standard clinical procedures. No intervention will be given to the participants in CG. Participants in EG will perform PGT from the 28th GW to their delivery following the video guidance on mobile app. They will be instructed to download and install the app by research assistants.

The app provides health education and a PGT video. Watching the health education video, participants can learn the pelvic floor anatomy and function and are informed about the negative impact of pregnancy and delivery on PFM. The PGT video includes PFMT and GPR programs designed collaboratively by the urogynecologists and the sports experts. The GPR combines global posture and respiratory training with PFMT to enable participants to exercise PFMT while posturing.

PFMT mainly focuses on voluntary contraction and relaxation of PFM around urethra, vagina and rectum. It provides instruction on coordinating PFM contraction and relaxation by exhalation and inhalation of a breathing circle, respectively, while avoiding the involvement of abdominal muscles. Participants need to contract the PFM first with moderate strength and upholding for 6–8 s, followed by 6–8 s PFM relaxation (the primary PFMT procedure), then repeat primary procedure five times to train the type I muscle fibers. As the second step, participants are asked to do quick maximum PFM contraction and relaxation in 1 s for five times, followed by 10 s of relaxation (the secondary PFMT procedure). The secondary PFMT procedure will be repeated for eight times to train the type II muscle fibers. Both the primary and secondary PFMT procedures need to be repeated for three sets in an exercise circle. Participants in EG need to perform PFMT twice a day following the instruction of the video program. 

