As we all know, mobile phones are becoming increasingly common, thus the app-based video guidance is easy to achieve with the aid of mobile devices. During the COVID-19 pandemic, adoption of the mobile-device-based PGT video program and Zoom meetings will not only enable the participants to perform PFMT and GPR safely at home, and increase participants’ interests for exercise, but also improve the compliance of participants, because participants can easily perform the 10-min PFMT session in any spare time and at any place. The automatic frequency recording design of the PFMT software is expected to provide better supervision on the compliance. 

This protocol is designed according to referring guidelines, consensus and high-quality studies. As a multicenter RCT, it will involve ten hospitals including tertiary hospitals and maternity hospitals located in several provinces, purposed to achieve more convincing results than other single center protocols [31,32]. 

The possible limits of this trial are that there will be no comparison of the virtual guidance and supervision versus the face-to-face ones because of the COVID-19 pandemic, and that the data may be contaminated due to no effective way to limit the participants in the control group doing PFMT personally. Another limitation of the trial is that the long follow-up time may increase the amount of the missing data.

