## Figures and Tables

**Figure 1 ijerph-18-12929-f001:**
[figure not shown]
Study flow.

**Table 1 ijerph-18-12929-t001:** Baseline screening, assessment, and follow-up schedule.

	At Pregnancy				At Postpartum			
	<16th Week	28th Week	37th Week	Delivery	6th Week	3rd Month	6th Month	12th Month
Follow-up schedule (week)	0	± 1	± 1	± 1	± 1	±2	± 2	± 2
Informed consent	•							
Demographic data collection	•							
Urinary leakage symptoms	•	•	•	•	•	•	•	•
Training frequency	•	•	•	•	•	•	•	•
Pb and gh	•		•					
Stress test	•		•		•	•	•	•
POP-Q staging					•	•	•	•
The modified Oxford Scale	•		•		•	•	•	•
The duration of the second labor stage				•				
The perineal laceration classification				•				
VAS				•				
Fetal/natal conditions	•	•	•	•				
Pelvic floor ultrasound	•				•	•	•	•
Pelvic floor electrophysiological test					•	•	•	•
PISQ-12	•				•	•	•	•
ICIQ-UI SF		▲	▲		▲	▲	▲	▲
OABSS		▲	▲		▲	▲	▲	▲
I-QOL		▲	▲		▲	▲	▲	▲

•: Indicates mandatory items; ▲: Investigator will decide whether to perform the test according to clinical signs or clinical evaluation. Pb: perineal body; gh: genital hiatus; POP-Q: pelvic organ prolapse quantitation; VAS: visual analog scale; PISQ-12: Prolapse/Urinary Incontinence Sexual Questionnaire short form; ICIQ-UI SF: the International Consultation on Incontinence Questionnaire-urinary incontinence short form; OABSS: Overactive Bladder Symptom Scores; I-QOL: the Incontinence Quality of Life.

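### Read naturally, the protocol reveals allocation at the consent visit before 16 weeks but starts the exercise programme at 28 weeks, leaving about 12 weeks of open allocation with no exercise scheduled

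*Protocol article*

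**What the plan says.** Four places in the protocol article fix the timing.

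- **Enrolment.** Section 2.2 admits women before the 16th gestation week (GW). Section 2.6 collects the baseline questionnaire at 16 GW or earlier. Table 1 marks informed consent only in its first column, the visit before week 16.
- **Disclosure.** Section 2.4: "Eligible women are informed of grouping allocation via opening the sealed envelope after signing the informed consent". No visit is named. The same section says that participants and the clinicians engaged in the intervention cannot be blinded, and that those who evaluate patients or analyse data are masked.
- **Start of exercise.** Section 2.5: "Participants in EG will perform PGT from the 28th GW to their delivery following the video guidance on mobile app". For controls: "No intervention will be given to the participants in CG". Background care is shared: "All participants in EG and CG will have same routine obstetric prenatal care following the standard clinical procedures".
- **Stage of the trial.** The Abstract says "The experimental stage will be from the 16th gestation week (GW) to the 12th month postpartum", although no exercise is scheduled before 28 GW.

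Section 2.3 records a woman as having dropped out after miscarriage, serious complications or missing all follow-ups. Section 2.9 analyses by intention to treat with multiple imputation, followed by a sensitivity analysis that counts missing outcomes as failures and one on complete cases. Section 3 concedes that "the data may be contaminated due to no effective way to limit the participants in the control group doing PFMT personally".

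**The concern.** Randomising well before the intervention starts has a cost when participants cannot be blinded. Here the protocol gives no reason for disclosing the arm so early, and three consequences follow.

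1. A woman who miscarries or withdraws between enrolment and 28 GW has had no scheduled exercise in either arm. She is still in the intention-to-treat set, and her 6-week postpartum outcome must be imputed. In one sensitivity analysis she counts as a case of stress urinary incontinence (SUI).
2. Withdrawal during the gap happens with the arm known. Controls who hoped for the programme may leave more often than women assigned to it. Loss that differs by arm can bias the comparison, whereas loss before randomisation cannot.
3. The period in which women can start pelvic floor training on their own, knowing their arm, is lengthened.

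In addition, the leakage question at 28 GW, the only leakage record scheduled when exercise begins, becomes a post-randomisation report by a woman who knows her arm. It then cannot serve as a baseline covariate.

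**Working it through.** **The plan's own figures.** Inputs from section 2.8: 25.7% against 15%, two-sided 0.05, power 90%, dropout 20%. With unpooled variance, n per group = (1.960 + 1.282)² × (0.257 × 0.743 + 0.15 × 0.85) / 0.107², which rounds up to 293. Then 293 / 0.8 = 366.25, rounded up to 367 per group and 734 in total. The sample size is reproduced and is not in question.

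**Length of the gap.**
- Nominal: 28 − 16 = 12 weeks, and longer for women enrolled earlier.
- Shortest: enrolment at exactly 16 GW (section 2.6) with the 28-week visit one week early (Table 1 allows ±1 week) gives 27 − 16 = 11 weeks, if exercise starts at that visit.
- For comparison, section 3 gives the training period as 12 weeks, so the gap is about as long as the intervention.

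**Losses in the gap.** Section 2.8 does not say over what period the 20% dropout accrues. Assume a constant loss rate from 16 GW, delivery at 40 GW, and a 12-week gap. The fraction lost before 28 GW is 1 − 0.8^(12/T), where T is the accrual period in weeks.

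| Assumed accrual of the 20% | T (weeks) | Lost before 28 GW | Of 734 |
|---|---|---|---|
| to 6 weeks postpartum | 24 + 6 = 30 | 1 − 0.8^(12/30) = 8.5% | 63 |
| to 12 months postpartum | 24 + 52 = 76 | 1 − 0.8^(12/76) = 3.5% | 25 |

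The dropout allowance is 0.20 × 734 ≈ 147 women, so the gap would use 25/147 = 17% to 63/147 = 43% of it.

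**Effect on the missing-as-failure analysis.** Suppose the gap losses are equal in both arms and the remaining women have the planned rates. Counting the lost women as SUI cases shrinks the planned difference by the fraction lost: 10.7 × (1 − 0.035) = 10.3 points, or 10.7 × (1 − 0.085) = 9.8 points. This is dilution from the gap alone and affects that sensitivity analysis only.

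**Number reaching the endpoint if the envelope is opened at 28 GW.** With 734 enrolled and the same loss rates, 734 − 63 = 671 to 734 − 25 = 709 would be randomised. The women no longer randomised would not have reached the endpoint anyway. With 20% lost by 6 weeks postpartum, 734 × 0.8 = 587 remain under either timing, against the 586 required.

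**The case against.** The strongest reply is that the key date is inferred. Section 2.4 says only that the envelope follows consent, Table 1 has no randomisation row, and the study-flow figure is not available here. That stands, and the point is worded accordingly. The enrolment visit is the natural reading because no later allocation step appears anywhere.

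Several stronger readings are tempting, and the documents do not support them.

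- *Everyone in the trial is unblinded for the whole gap.* Section 2.4 masks evaluators and analysts. The exposure concerns participants and intervention staff.
- *The arms are identical until 28 GW.* The app includes health education, and its installation is not dated. If it is installed at enrolment, the arms differ in education earlier, though not in scheduled exercise.
- *Contamination can be sized by letting some fraction of controls gain the full benefit.* That measures total contamination and not the increment from early disclosure. Controls would know their arm from 28 GW to delivery in any case, and enrolled women could start training on their own before allocation. Section 2.6 also records training frequency for all participants, so self-training is measured.
- *Leakage that begins before 28 GW biases the result.* Randomisation balances it in expectation, and the aim in section 1 is prevention of postpartum SUI, so mid-pregnancy leakage does not void the question.
- *The gap losses reduce the evaluable number.* They do not, because those women would be lost under either timing. The possible harm lies in differential loss and in imputation, and the documents quantify neither.

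**Conclusion.** The point holds as a design weakness. It is not a contradiction or a calculation error. On the natural reading, about 12 weeks (about 11 at the shortest) pass with the arm known to women and intervention staff and no exercise scheduled. Intention to treat remains valid. The cost has three parts: post-randomisation losses that the exercise could not have affected and that must be imputed, the possibility of withdrawal that differs by arm, and a longer window for self-started training.

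The only size that can be offered is conditional. Under a constant loss rate, 3.5% to 8.5% of 734 women (25 to 63) would be lost in the gap, depending on whether the 20% dropout runs to 12 months or to 6 weeks postpartum. No figure for contamination or for differential withdrawal can be derived from the documents. A change is worth making because it is cheap, not because the primary comparison would otherwise fail.

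**What to change.** Keep consent, screening and baseline assessment before 16 GW. Then:

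1. Open the envelope at the existing 28-GW visit, after leakage symptoms are recorded and before the app is installed. Add a randomisation row to Table 1 and name the visit in section 2.4.
2. Define the intention-to-treat set as women randomised at that visit, and state in section 2.8 that 734 is the number enrolled.
3. Use symptom-reported leakage at 28 GW as a baseline covariate in a supportive analysis. Describe it as symptoms only: Table 1 schedules no stress test at that visit, so it does not match the endpoint definition in section 2.7.
4. Align the Abstract by separating enrolment before 16 GW from the randomised stage starting at 28 GW.

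**Cost.** A short amendment and a site instruction, with no new visit or procedure. Fewer than 734 women are randomised (about 671 to 709 on the assumptions above), but the number expected at 6 weeks postpartum is unchanged. Allocation, app installation and class assignment all fall at one visit with a ±1 week window, so sites need to prepare for it. Envelopes are matched to study IDs. They should be numbered in order of randomisation and not of enrolment, so that women lost before 28 GW do not leave gaps in the blocks of four.

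If early disclosure is intended, the protocol should give the reason, date the app installation, and report losses before and after 28 GW by arm.
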